### Laboratory analysis

Fecal samples will be analyzed by direct observation of eggs and/or larvae by microscopy and egg counting by the Kato-Katz technique. Direct microscopy is the diagnostic standard in areas with limited resources. The Kato-Katz method is used to estimate the intensity of infection by *Ascaris lumbricoides*, hookworms and *Trichuris trichiura*. Although this method is more sensitive than direct microscopy, it requires more time and labor to detect geohelminth eggs [25, 26]. Once the procedures have been carried out and the results obtained, the remaining stool samples will be aliquoted and stored at − 80 °C.

In the second sample, molecular detection of helminths by polymerase chain reaction (qPCR) will be performed on specimens with helminths detected (i.e., clinical resistance) in order to determine the presence of resistance markers at the genetic level.

Direct observation: In a properly labeled slide, 0.5 g of feces will be applied with a wooden applicator and 20 µL of saline solution will be added. The first observation will be made from left to right, then the procedure will be repeated with 20 µL of Lugol’s solution added. Both observations will be made with the 10× and 40× objectives in order to qualitatively identify the absence or presence of helminths (*Ascaris lumbricoides*, *Trichuris trichiura*, hookworms, and *Strongyloides stercoralis*).Kato-Katz method: Two grams of feces will be placed on a smooth and sterile surface, covered with a piece of nylon and pressed with a flat-edge plastic applicator. The filtered feces will then be placed in the center of a 41.7 mg template on a slide until the hole is filled, after which the template will be removed and the sample will be covered with a cellophane sheet previously imbued in a glycerol-blue solution of methylene, and pressure will be applied until the sample is distributed homogeneously. After a 30-min incubation, eggs counts will be carried out using the 10× objective and a cell counter, the total number of eggs counts per species will be reported in eggs per gram (epg) and will be multiplied by 24 (41.7 mg template) [27], and the results of each parasite found will be recorded and reported quantitatively. This procedure will be performed on the 4 samples per subject collected throughout the study [28].STH infection by qPCR: To measure the intensity of the infection, quantitative polymerase chain reaction (qPCR) will be used in such a way that the Kato-Katz variability between users is reduced and the sensitivity of the detection of low-grade parasitic infections is increased [29, 30]. Real-time multiplex qPCR will be performed on positive samples (Day 0) for helminths that were identified by direct observation and Kato-Katz for the simultaneous detection of *Ascaris lumbricoides*, *Trichuris trichiura*, *Necator americanus*, *Ancylostoma duodenale*, and *Strongyloides stercoralis* [31]. If the sample from Day 0 is negative, the sample from Day 15 will be analyzed if it is positive for helminths. Amplification will be performed in a Quant Studio 7 Flex thermocycler (Applied biosystems) in a total volume of 25 µL using GoTaq® qPCR Probe Master Mix (Promega, USA) and 5 µL of fecal DNA. There will be two multiplex qPCR assays (STH1 and STH2); STH1 will be used to detect *Ascaris lumbricoides*, *Trichuris trichiura* and *Strongyloides stercoralis*, while STH2 will be used for the 3 species of hookworms. The cycling conditions for both cases will be the following: 1 cycle at 95 °C for 5 min, 40 cycles at 95 °C for 10 s and 1 cycle at 60 °C for 60 s. The primers will be the same ones used by Azzopardi et al. [32] which can be seen in Table 1.**Table 1 Tab1:** Primers used in multiplex qPCR analysis of stool samples by STH1 and STH2

qPCR	Target	Primer	Sequence (5′–3′)	Size (bp)	Gene detected	Final conc. (nM)
STH1	*Strongyloides stercoralis*	Strongy-F	GAATTCCAAGTAAACGTAAGTCATTAGC	101	18S	100
		Strongy-R	TGCCTCTGGATATTGCTCAGTTC			100
		Strongy-P	FAM-ACACACCGG/ZEN/CCGTCGCTGC-IBFQ			50
STH1	*Trichuris trichiura*	Tri-F	TTGAAACGACTTGCTCATCAACTT	76	18S	100
		Tri-R	CTGATTCTCCGTTAACCGTTGTC			100
		Tri-P	CY5-CGATGGTAC/TAO/GCTACGTGCTTACCATGG-IBRQ			50
STH1	*Ascaris lumbricoides*	Asc-F	GTAATAGCAGTCGGCGGTTTCTT	87	Internal transcribed spacer 1	100
		Asc-R	GCCCAACATGCCACCTATTC			100
		Asc-P	HEX-TTGGCGGAC/ZEN/AATTGCATGCGAT-IBFQ			50
STH2	*Ancylostoma* spp.	Anc-F	CGGGAAGGTTGGGAGTATC	104	Internal transcribed spacer 1	100
		Anc-R	CGAACTTCGCACAGCAATC			100
	*A*. *duodenale*	Aduo-P	HEX-TCGTTAC + T + GGGTGACGG-IBFQ			50
	*A*. *ceylanicum*	Acey-P	FAM-CCGTTC + CTGGGTGGC-IBFQ			50
STH2	*Necator americanus*	Nec-F	CTGTTTGTCGAACGGTACTTGC	101	Internal transcribed spacer 2	100
		Nec-R	ATAACAGCGTGCACATGTTGC			100
		Nec-P	CY5-CTG+TA+CTA+CG+CAT+TGTATAC-IBRQ			50
STH1 Y STH 2	*Phocine herpes virus*	PhHV-F	GGGCGAATCACAGATTGAATC		gB gene	100
		PhHV-R	GCGGTTCCAAACGTACCAA			100
		PhHV-P	Cy5-TTTTTATGTGTCCGCCACCATCTGGATC-BHQ2			50DNA extraction from STH: Nucleic acid extraction will be performed using the purification method by column centrifugation and cell disruption by bead beater, which consists of lysing the sample by mechanical disruption. The guidelines of the modified protocol of the QIAmp Fast DNA Stool mini kit (CAT 51604) will be followed, which consists of 4 phases (lysis, filtering, washing and elution), with an approximate time of 60 min for 8 samples. To evaluate the quality of the extraction and the efficiency of the amplification, extrinsic controls (MS2 and PhHV) will be added to each sample during the lysis phase. Subsequently, the DNA obtained will be stored at − 20 °C for the following processes or at − 80 °C for prolonged storage.

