The efficacy of albendazole is variable against *Trichuris trichiura* compared to other anthelmintics; the cure rate ranges between 2.6 and 64.5% [8] and the egg reduction rate ranges between 7 and 83.1%. However, high cure rates of *Trichuris trichiura* are observed in some contexts [9–11]. In a study conducted in the Peruvian Amazon, an open-pair randomized trial was conducted in fifth-grade children from 18 primary schools (9 intervention and 9 control). Intensity of *Ascaris lumbricoides* infection at follow-up was 58% lower in children from intervention schools, a significant reduction as compared to children from control schools (RR = 0.42; 95% CI 0.21 to 0.85), but no significant changes were observed in the intensity of hookworm or *Trichuris trichiura* [12]. In another study from Peru, a total of 1193 school-age children were dewormed with a single dose of Albendazole (400 mg). Of the 909 children who tested positive for at least one STH infection, a random sample of 385 were followed up 2 weeks later with a second stool sample. The efficacy of albendazole was variable, with an egg reduction rate of 99.8% for *Ascaris lumbricoides* (95% CI 99.3–100); 93.6% for hookworm (95% CI 88.2–96.6), and 72.7% for *Trichuris trichiura* (95% CI 58.5–79, 1) [13]. In many cases treatment with albendazole alone appeared inadequate, especially for *Trichuris trichiura*. Other interventions such as combined therapy have been evaluated in other contexts. Ivermectin results in higher cure rates than albendazole and is well tolerated. The benefits of ivermectin for helminth infections would depend on the amount of resistance present [14–16].

Large-scale interventions to control soil-transmitted helminth infections at the community level with anthelmintic drugs such as albendazole have the potential to exert selective pressures which may favor the development of drug resistance, which could significantly reduce the benefits provided by deworming programs. Drug resistance in parasitic nematodes is caused by a single nucleotide polymorphism (SNP) in the β-tubulin gene at codon positions 200 (T → A), 167 (T → A) or 198 (A → C) [17].

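### The qPCR assigned to find genetic resistance markers targets only species-identification regions, and Table 1 as printed gives its internal control the same dye as Trichuris and Necator

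*Protocol article*

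**What the plan says.** **Resistance markers.** The Background states: "Drug resistance in parasitic nematodes is caused by a single nucleotide polymorphism (SNP) in the β-tubulin gene at codon positions 200", and adds codons 167 and 198. The Laboratory analysis section then says of the second sample that "molecular detection of helminths by polymerase chain reaction (qPCR) will be performed on specimens with helminths detected (i.e., clinical resistance") and gives the purpose as "in order to determine the presence of resistance markers at the genetic level". The same section describes two multiplex assays, STH1 and STH2, and Table 1 prints their primers, probes and target genes. The target for Ascaris and for Ancylostoma, for example, is "Internal transcribed spacer 1".

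**Internal control.** Table 1 lists the PhHV control for both STH1 and STH2 with the probe "Cy5-TTTTTATGTGTCCGCCACCATCTGGATC-BHQ2". The Trichuris probe in STH1 is "CY5-CGATGGTAC/TAO/GCTACGTGCTTACCATGG-IBRQ" and the Necator probe in STH2 is "CY5-CTG+TA+CTA+CG+CAT+TGTATAC-IBRQ". The DNA extraction paragraph says that "extrinsic controls (MS2 and PhHV) will be added to each sample during the lysis phase".

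**Use of the results.** The Statistical analysis section converts Ct to eggs per gram (EPG) for Ascaris, Trichuris, N. americanus and A. duodenale, and compares Ct values with a paired t-test.

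**The concern.** The marker statement gives an assay a purpose that its design cannot serve. Albendazole resistance is the first major outcome. The Background reports albendazole cure rates for Trichuris from 2.6% to 64.5%, so a stool still positive at 15 to 25 days does not by itself distinguish genetic resistance from a drug that works poorly against that species. The marker test is the only genetic evidence the article promises. If the text stands, a positive STH1 or STH2 result on a second sample could be reported as evidence about resistance genotype, when it only confirms that a species is present.

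The dye question is a separate, conditional matter. Two probes with the same dye in one well cannot be told apart by colour. If the control is read in the same well, a Cy5 signal could come from the worm or from the control. The Ct and EPG values for Trichuris and Necator would then be uncertain, and the control could not reveal failed extraction or inhibition in a sample that contains either species.

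**Working it through.** The protocol gives no figure on this point to reproduce. The check compares one part of the text with another, followed by one illustration.

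**Step 1: targets against markers.** The Background names β-tubulin codons 167, 198 and 200. Table 1 gives these helminth targets:

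| Assay | Species | Gene | Probe dye |
|---|---|---|---|
| STH1 | Strongyloides stercoralis | 18S | FAM |
| STH1 | Trichuris trichiura | 18S | Cy5 |
| STH1 | Ascaris lumbricoides | ITS1 | HEX |
| STH2 | A. duodenale | ITS1 (shared Ancylostoma primers) | HEX |
| STH2 | A. ceylanicum | ITS1 (shared Ancylostoma primers) | FAM |
| STH2 | Necator americanus | ITS2 | Cy5 |
| both | PhHV control | gB | Cy5 |

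Of the five helminth primer pairs, 0 target β-tubulin. The article describes no SNP probe or sequencing step. The Statistical analysis section covers prevalence, Ct, EPG, cure rate and egg reduction, with no genotype analysis.

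**Step 2: dyes within each multiplex.**
- STH1: FAM = Strongyloides; HEX = Ascaris; Cy5 = Trichuris and PhHV.
- STH2: FAM = A. ceylanicum; HEX = A. duodenale; Cy5 = Necator and PhHV.

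Two of the six helminth probes share the control's dye. Two of the four species with an EPG conversion (Trichuris and N. americanus) are therefore exposed.

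**Step 3: what a shared well would do to EPG (illustration only).** The article does not give the control's Ct, so 28 to 34 is an assumption. The conversions are read as powers of ten:

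- Trichuris: EPG = 10^((Ct − 36.73)/−3.288)
- N. americanus: EPG = 10^((Ct − 35.02)/−3.641)

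| Assumed control Ct | Read as Trichuris EPG | Read as Necator EPG |
|---|---|---|
| 28 | 452.0 | 84.7 |
| 30 | 111.4 | 23.9 |
| 32 | 27.5 | 6.8 |
| 34 | 6.8 | 1.9 |

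For Ct 30, the Trichuris exponent is (30 − 36.73)/−3.288 = 2.047, and 10^2.047 ≈ 111. These are the values a sample free of that species (for example, one positive only for Ascaris) would appear to have if the control signal were read as worm DNA. They show how the error would behave and do not estimate its size in this study.

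**The case against.** **A condensed article.** The full protocol may contain a β-tubulin assay, and the article stores extracted DNA for later processes. This stands as a limit: it cannot be said that the study will produce no marker data. It does not rescue the sentence, because the article does not defer the markers to another method. It assigns them to the helminth-detection qPCR, whose sequences it prints in full.

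**The control may not share a well.** Table 1 lists PhHV under both multiplexes but describes no plate layout, and the text on what STH1 and STH2 detect names helminths only. A second control, MS2, is added to samples yet has no row in the table, so the table does not list every control assay. The PhHV row also has a different quencher and no amplicon size, which would fit a separate reaction or a copying error. This stands too: the dye clash is a feature of the table as printed, not a demonstrated assay failure.

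**Stronger readings.** A reader might infer that the qPCR as a whole is unusable, or that its specificity for Trichuris and Necator falls to zero. The documents do not support either. Ascaris, Strongyloides, A. duodenale and A. ceylanicum have dyes that the control does not use, and the loss of specificity presupposes a shared well. A reader might also infer that the resistance outcome fails or must be renamed. The Sample size section bases it on any helminth in a follow-up sample, and the Laboratory analysis section already calls it clinical resistance. Kato-Katz counts are planned on all four samples, so cure rate and egg reduction for Ascaris, hookworm and Trichuris can be obtained without qPCR. Renaming the outcome would be a matter of preference.

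**Conclusion.** The marker purpose is wrong as written. By the protocol's own account of where the markers lie, STH1 and STH2 cannot determine them, and this needs no assumption beyond the Background, the Laboratory analysis section and Table 1. The defect is confined to that stated purpose and to any genetic conclusion drawn from these assays.

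The dye assignment needs correction or clarification. Its effect is conditional: if PhHV is read in the same well, the Trichuris and Necator Ct values, the EPG derived from them and the control read-out are confounded. If it runs separately, or the Cy5 label is a misprint, only the table is wrong. No numerical loss can be fixed from the document. Neither point undermines the microscopy and Kato-Katz outcomes, so both should be corrected but neither threatens the study's main results.

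**What to change.** 1. Delete the resistance-marker purpose from the qPCR on second samples, describe it as species detection and quantification, and draw no genetic-resistance conclusion from it. This costs one sentence. If markers are to be kept, name a β-tubulin codon 167/198/200 SNP assay on the stored DNA. That means additional laboratory work, but the plan already stores frozen DNA and stool aliquots.
2. Give PhHV a dye unused by the helminth probes in each multiplex, or state that it runs in a separate reaction, and correct Table 1 to match. This costs one relabelled probe or one extra control well per sample and assay. If the Cy5 entry is a misprint, it costs only the table correction.

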### Statistical analysis

Data will be analyzed in Access using Stata, using chi square, Fisher’s exact, and Wilcoxon tests to compare frequencies between groups. To analyze the data from direct observation and quantification by the Kato-Katz method, descriptive statistics will be used, to report the prevalence found in percentages. For the sociodemographic and clinical data of the study population, measures of central tendency and dispersion will be used for the quantitative variables and measures of relative frequency for the qualitative variables. Comparisons will also be made between sample 1, sample 2, sample 3 and sample 4 to determine the positivity of each species of parasite found using the Yates chi-square test, setting a significance level of p < 0.05.

The sociodemographic variables will be compared with the parasite load and presence/absence of parasites, using a multiple logistic regression model (univariate t-test), to determine the variables statistically associated with infection by *Ascaris lumbricoides*, *Trichuris trichiura* and hookworms.

The quantification performed with the Kato-Katz method will be compared with the Ct value (Ct threshold) of the multiplex qPCR, by converting Log10 of the absolute egg count per stool sample, in order to estimate the absolute egg counts in eggs per gram (EPG) in the DNA extractions, using the following formula [33]:$${\text{EPG}}\;{\text{Ascaris}} = 10\left( {{\text{Ct}} - 36.97} \right)/ - 3.489,$$$${\text{EPG}}\;{\text{Trichuris}} = 10\left( {{\text{Ct}} - 36.73} \right)/ - 3.288,$$$${\text{EPG}}\;N.\;americanus = 10\left( {{\text{Ct}} - 35.02} \right)/ - 3.641,$$$${\text{EPG}}\;A.\;duodenale = 10\left( {{\text{Ct}} - 35.02} \right)/ - 3.641.$$

To determine treatment efficacy, the prevalence will be measured before and after receiving treatment and compared using the Yates chi-square test. For calculations of cure rate and intensity of infection obtained from qPCR, only data from positive results before taking the first dose will be included [34].

The cure rate will be measured using the following formula:$$\frac{{\# \;{\text{positive}}\;{\text{for}}\;{\text{helminths}}\;\left( {{\text{pretreatment}}} \right) - \# \;{\text{negative}}\;{\text{for}}\;{\text{helminths}}\;\left( {{\text{post}}\;{\text{treatment}}} \right)}}{{\# \;{\text{cases}}\;{\text{positive}}\;{\text{for}}\;{\text{helminths}}\;\left( {{\text{pretreatment}}} \right)}} \times 100.$$

Intensity of infection will be measured using the following formula:$$\frac{{{\text{mean}}\;{\text{egg}}\;{\text{count}}\;\left( {{\text{pretreatment}}} \right) - {\text{mean}}\;{\text{egg}}\;{\text{count}}\;\left( {{\text{post}}\;{\text{treatment}}} \right)}}{{{\text{mean}}\;{\text{egg}}\;{\text{count}}\;\left( {{\text{pretreatment}}} \right)}} \times 100.$$

And the calculation of the rate of reduction of eggs by helminth species:$$\frac{{\left[ {1 - {\text{mean}}\;{\text{egg}}\;{\text{count}}\;{\text{in}}\;{\text{EPG}}\;\left( {{\text{post}}\;{\text{treatment}}} \right)} \right]}}{{{\text{mean}}\;{\text{egg}}\;{\text{count}}\;{\text{in}}\;{\text{EPG}}\;\left( {{\text{pretreatment}}} \right)}} \times 100.$$

In addition, a comparison of the cycle threshold (Ct) by qPCR will be made using the Student’s t-test for paired samples.

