### Sample size

Sampling will be carried out throughout the jurisdiction of the 6 de Octubre Health Center, which includes rural, peri-urban and urban areas, with a total potential study population of 3379 children ages 2 to 11 years based on health center databases. Based on this study population of 3379 children aged 2 to 11 years, to measure clinical resistance to albendazole a sample of 380 children was needed. This calculation was made in Epi Info Version 7.2 applying a type I error of 5% and assuming 50% prevalence of helminths in children, 25% frequency of *Trichuris trichiura* in children with helminths, 50% resistance to albendazole based on detection of any helminth in a follow-up sample and adjusting for 10% loss to follow-up for study participants.

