### Recruitment of participants

To identify eligible children for the study, a community census is being conducted in the catchment area of the Centro de Salud 6 de Octubre, which includes rural, peri-urban and urban areas. Rural areas are defined as streets located on the opposite side of the Itaya river from the city of Iquitos, which is a flood prone area without basic services, electricity and drinking water. Peri-urban areas are located on the Iquitos side of the river and extend into the river, with houses on stilts or raft houses that float on the surface of the river. Many of these houses already have electricity and drinking water, and they are usually located around the health center. Another part of the study community is located in the urban area of Iquitos, with concrete houses that all basic services and access to food markets, etc.

For enrollment in rural areas, a sweep strategy will be applied, meaning that we will look for children who meet the inclusion criteria throughout the community. For the peri-urban area homes without an address (located on rafts) we will also apply the same strategy. In the peri-urban and urban area where there are well-defined maps with streets and addresses, we will recruit candidates with numerical codes from the community census based on a random number generator, starting from the first block and then moving forward clockwise to the next block.

Once the first randomly selected child of any age between 2 and 11 years has been recruited, enrollment will continue in the same way until the established strata are completed: age 2 years = 36 children; 3 years = 36 children; 4 years = 36; 5 years = 32 children; 6 years = 33 children; 7 years = 34 children; 8 years = 35 children; 9 years = 36 children; 10 years = 33 children; 11 years = 34 children. Once all the blocks of the study community have been sampled, if the target number of participants for each stratum were not completed, the process will be repeated from the beginning and thus complete the corresponding sample for each age group.

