## Data and specimen collection (see Fig. 1 for overview of study visits and procedures)

Following informed consent, demographic data will be collected, including housing characteristics, general caregiver information, and information on hygiene and childcare. Weight and height measurements will be performed by a member of the on-site investigation team, and a stool collection container will be provided to the caregiver [19]. Fresh feces (10–20 g) will be collected from each participant and the date and time of specimen collection will be recorded upon retrieval. At the end of the day specimens will be transported to the laboratory in a biological sample transport box with ice at the end of the day, for analyses that will be carried out within the next 24 h.

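### Siblings can be enrolled and several exposures are shared by a household, but neither the risk-factor model nor the sample size of 380 allows for clustering within households

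*Protocol article*

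**What the plan says.** All places are in the protocol article.

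- **Recruitment of participants.** Rural areas and raft homes without an address are covered by a sweep that looks for eligible children throughout the community. In mapped urban and peri-urban blocks, children are drawn from coded census entries with a random number generator. In both cases "enrollment will continue in the same way until the established strata are completed"; the strata are single years of age from 2 to 11. Neither this section nor the inclusion criteria under Study design restricts the number of children per household.
- **Data and specimen collection.** Demographic data are collected, "including housing characteristics, general caregiver information, and information on hygiene and childcare".
- **Statistical analysis.** "The sociodemographic variables will be compared with the parasite load and presence/absence of parasites", using multiple logistic regression, to find the variables associated with infection by each species. Chi-square, Fisher's exact and Wilcoxon tests compare groups. No household term or clustered variance is mentioned.
- **Sample size.** The area is described "with a total potential study population of 3379 children ages 2 to 11 years", and "to measure clinical resistance to albendazole a sample of 380 children was needed". The calculation is described as "applying a type I error of 5% and assuming 50% prevalence of helminths in children", with further assumptions on the share of *Trichuris*, on resistance (50%) and on loss to follow-up (10%). No design effect is named.

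**The concern.** Housing and caregiver variables take one value per household, and hygiene and childcare items largely do. When such a variable is tested against an outcome that is positively correlated among children of the same home, two siblings carry less information than two unrelated children. A logistic regression that treats children as independent then gives standard errors that are too small, intervals that are too narrow and p-values that are too low for exactly these factors. Associations of housing or caregiver characteristics with infection would be declared more often than the nominal level implies.

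The age quotas do not prevent this, because brothers and sisters of different ages fill different strata. The same correlation makes intervals around prevalence, resistance and reinfection too narrow if they are computed as for a simple random sample.

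**Working it through.** **1. The plan's own figure.** Inputs from the Sample size section: N = 3379, p = 0.5, 5% error (z = 1.96), 10% loss. The section gives no precision, so a half-width d = 0.05 is assumed. With a design effect (DEFF) of 1:

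n = N·p(1 − p) / [(d²/z²)(N − 1) + p(1 − p)]
= 844.75 / [(0.0025/3.8416) × 3378 + 0.25]
= 844.75 / 2.448
= 345.

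345 × 1.10 = 379.5, that is 380. The age quotas also sum to 345 (36 + 36 + 36 + 32 + 33 + 34 + 35 + 36 + 33 + 34). So 380 agrees with a precision calculation for independent children; the *Trichuris* share is not needed to reach it.

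**2. Effect of clustering.** Let m be the number of sampled children per household and ICC the intraclass correlation of infection. Neither is in the article, so both are assumed.

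- DEFF = 1 + (m − 1) × ICC
- True two-sided error of a nominal 5% test on a factor constant within households = 2 × [1 − Φ(1.96/√DEFF)]
- Effective sample size = 345/DEFF
- Half-width for a proportion of 50% among 345 of 3379 children = 1.96 × √[(0.25/345)(1 − 345/3379) × DEFF]

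| m | ICC | DEFF | True error | Effective n | Half-width (points) |
|---|---|---|---|---|---|
| 1 | any | 1.00 | 5.0% | 345 | 5.0 |
| 1.2 | 0.05 | 1.01 | 5.1% | 342 | 5.0 |
| 1.2 | 0.4 | 1.08 | 5.9% | 319 | 5.2 |
| 2 | 0.2 | 1.20 | 7.4% | 288 | 5.5 |
| 2.5 | 0.3 | 1.45 | 10.4% | 238 | 6.0 |
| 3 | 0.4 | 1.80 | 14.4% | 192 | 6.7 |

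**3. Where the low end comes from.** 380/3379 is about 11%. If selection were random and each home had three eligible children (assumed), a sampled child would bring on average 2 × 0.11 ≈ 0.2 sampled siblings, so m is about 1.2. A sweep from home to home can give a larger m; the share of the sample that comes from sweep areas is not stated.

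**4. Check by simulation.** 345 children, 50% infected, a household-level exposure unrelated to infection, 1,500 runs per setting (simulation error about 0.6 points). The table gives the share of runs declared significant at 5%.

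| Sampled households giving one child | ICC | Ordinary logistic | Household-robust errors |
|---|---|---|---|
| 100% | 0.3 | 5.5% | 5.5% |
| 70% | 0.1 | 5.6% | 4.9% |
| 70% | 0.3 | 8.4% | 5.1% |
| 45% | 0.1 | 6.6% | 5.4% |
| 45% | 0.3 | 9.5% | 5.1% |

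Both the direction of the effect and the remedy are confirmed. Rejection rates under ordinary regression rise with the correlation and with the share of multi-child homes; robust errors hold them close to 5%.

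**The case against.** The strongest reply is that the article is silent on the variance estimator rather than wrong. Multiple logistic regression is compatible with clustered standard errors, and a fuller protocol or analysis plan may specify them. That is fair for the regression taken alone. It does not cover the design: the printed sample size matches a calculation without a design effect, the recruitment rules are set out here without a household limit, and a household identifier has to be captured at enrolment.

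Four stronger readings are tempting, and the article does not support them.

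- *Siblings will certainly be enrolled, because the sweep takes every eligible child.* The sweep looks for eligible children and enrolment ends when the quotas are full. Siblings, household size and a household rule are never mentioned. The text permits siblings; it does not say that they will enter.
- *The stated 5% error rate is not held.* The level of p < 0.05 is set for the comparison of samples 1 to 4, not for the regression. How far any nominal 5% test of a risk factor departs from its level depends entirely on m and ICC. At m of about 1.2 the error is 5.1% to 5.9%, which is negligible.
- *The sample size loses its error control.* The 380 is consistent with a precision calculation. Clustering widens that interval; it breaks no test.
- *All covariates take the full design effect.* Age and sex vary within a household, and hygiene or childcare may differ between children. The full effect applies only to factors constant within the home.

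It also stands that resistance and reinfection are the major outcomes, so the risk-factor model is not where the study's main conclusions are drawn.

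**Conclusion.** The point holds conditionally. As described, the plan allows several children per home, tests exposures that are shared within a home, and makes no allowance for this in the model or in the sample size. If infection is positively correlated within households, p-values and intervals for household-level factors will be too optimistic, and the precision of prevalence and resistance estimates somewhat overstated.

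The size cannot be fixed from the article. Over the assumed ranges the effect runs from almost nothing to serious. In the middle case (m = 2, ICC 0.2) it is moderate, with a half-width about half a point wider than assumed. The high end needs many multi-child homes and strong correlation, and is more plausible in sweep areas than in the randomly sampled blocks. With one child per household there is no problem. The half-widths refer to a proportion over all 345 children, not to the infected subgroup. This is a cheap improvement worth making, not a flaw that undermines the study.

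**What to change.** 1. State whether more than one child per household may enrol, and record a household identifier for every child at enrolment; the community census under way is a natural source.
2. Fit the risk-factor models with household-clustered robust standard errors (in Stata, `vce(cluster household)`), or by GEE or with a household random intercept.
3. Use the same clustering for confidence intervals of prevalence, resistance and reinfection.
4. Keep the target of 380 and restate the expected precision with an assumed design effect, for example 5.5 points at 1.20, rather than enrolling more children. Holding 5 points at that design effect would take 447 with the plan's own 10% inflation.

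The cost is one data field and one option in the analysis code. The downside is wider confidence intervals: by a factor of √1.20 ≈ 1.10 in the middle case and √1.80 ≈ 1.34 at the high end of the assumed range.

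### The four Ct-to-EPG conversions are printed as 10 times (Ct − intercept)/slope, not 10 to that power, so qPCR egg counts coded as printed would be capped near 100, negative at late Ct, and distorted

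*Protocol article*

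**What the plan says.** The Statistical analysis section of the protocol article compares Kato-Katz counts with the multiplex qPCR Ct value. It describes the step as made "by converting Log10 of the absolute egg count per stool sample", with the aim stated as "in order to estimate the absolute egg counts in eggs per gram (EPG) in the DNA extractions". The conversions follow:

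- Ascaris: "EPG}}\;{\text{Ascaris}} = 10\left( {{\text{Ct}} - 36.97} \right)/ - 3.489"
- Trichuris: "EPG}}\;{\text{Trichuris}} = 10\left( {{\text{Ct}} - 36.73} \right)/ - 3.288"
- N. americanus: "EPG}}\;N.\;americanus = 10\left( {{\text{Ct}} - 35.02} \right)/ - 3.641" (A. duodenale is printed with the same two constants)

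Read as mathematics, each is the number 10 multiplied by a bracket and divided by a slope. None carries a superscript.

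The Laboratory analysis section gives qPCR a definite role: "To measure the intensity of the infection, quantitative polymerase chain reaction (qPCR) will be used". The assay runs "40 cycles at 95 °C for 10 s", so Ct can go up to 40. The Statistical analysis section also plans an intensity of infection from qPCR in children positive before the first dose, and gives intensity as a relative fall in mean egg count.

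**The concern.** A standard curve fitted to log10 egg count has the form Ct = intercept + slope × log10(EPG). Solving for EPG requires 10 raised to the power (Ct − intercept)/slope. The printed form multiplies by 10 instead, which contradicts the log10 wording directly above it.

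The difference is one of kind. Each time Ct rises by one slope-length (about 3.3 to 3.6 cycles), the power form divides the egg count by 10, whereas the printed form subtracts 10 EPG. An analyst who coded the printed formulas would obtain qPCR egg counts that cannot agree with Kato-Katz for anything but very light infections, and egg reductions with no usable meaning.

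**Working it through.** **Inputs from the protocol article.** Intercept a and slope b: Ascaris 36.97 and −3.489; Trichuris 36.73 and −3.288; hookworm 35.02 and −3.641. Maximum Ct is 40. The Kato-Katz multiplier is 24 EPG per egg seen. The article states no result of the conversion, so there is no figure to reproduce.

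**Assumption.** The article gives no Ct values. Those used below are illustrative.

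**Step 1: which form is intended.** If the slopes come from log10 standard curves, the implied amplification efficiency is 10^(1/|b|) − 1. This gives 93.5% (Ascaris), 101.4% (Trichuris) and 88.2% (hookworm). Perfect doubling (100%) corresponds to 1/log10(2) = 3.32 cycles per ten-fold change, and the printed slopes lie close to that. The constants therefore agree with the log10 wording.

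**Step 2: values under each form.** Printed: 10 × (Ct − a)/b. Power: 10^[(Ct − a)/b]. Entries are Ascaris / Trichuris / hookworm, in EPG.

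| Ct | Printed form | Power form |
|---|---|---|
| 20 | 48.6 / 50.9 / 41.3 | 73,090 / 122,518 / 13,343 |
| 25 | 34.3 / 35.7 / 27.5 | 2,696 / 3,694 / 565 |
| 30 | 20.0 / 20.5 / 13.8 | 99 / 111 / 24 |
| 40 | −8.7 / −9.9 / −13.7 | 0.14 / 0.10 / 0.04 |

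**Step 3: ceiling.** The printed form is largest at Ct 0, which no sample can reach: 106.0 / 111.7 / 96.2 EPG. Dividing by 24 gives 4.4 / 4.7 / 4.0 eggs on a Kato-Katz slide.

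**Step 4: sign.** The printed form is negative once Ct exceeds the intercept, that is above 36.97 / 36.73 / 35.02. All three lie below 40.

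**Step 5: egg reduction.** Reduction = 1 − post/pre. In the printed form this is 1 − (Ct_post − a)/(Ct_pre − a). In the power form it is 1 − 10^[(Ct_post − Ct_pre)/b]. For Ascaris:

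| Assumed Ct, pre to post | Printed arithmetic | Printed | Power |
|---|---|---|---|
| 20 to 25 | 1 − 11.97/16.97 | 29.5% | 96.3% |
| 25 to 30 | 1 − 6.97/11.97 | 41.8% | 96.3% |
| 20 to 30 | 1 − 6.97/16.97 | 58.9% | 99.9% |
| 25 to 35 | 1 − 1.97/11.97 | 83.5% | 99.9% |
| 30 to 40 | 1 − (−3.03)/6.97 | 143.5% | 99.9% |

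For Ct 25 to 30, Trichuris gives 42.6% against 97.0% and hookworm 49.9% against 95.8%.

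**Step 6: is there a consistent direction?** No. On a uniform grid of Ct pairs (pre 15 to 34.75, post up to 40; an assumption, not a forecast), the printed reduction is less than half the power-form reduction in 37% / 36% / 30% of pairs, and equal to it or larger in 22% / 24% / 35%. Children who clear infection and count as zero change it again: for Ascaris, Ct 20 to 25 with half cleared gives 64.7% against 98.2%.

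**The case against.** **A lost superscript.** The exponent may have dropped out in typesetting, and the log10 sentence beside the formulas tells an attentive analyst what is meant. Negative counts would expose literal coding quickly. The harm arises only if the formulas are coded as printed. That limits the practical risk, but the equation markup is otherwise intact and all four formulas lack the power. The text as it stands is wrong and needs the same correction whatever the cause.

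**Reductions always understated.** A reader who looks only at Ct 25 to 30 might infer that qPCR reductions always come out at less than half their size. The documents give no Ct values, and steps 5 and 6 show mild understatement and overstatement as well, including reductions above 100%.

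**False resistance.** A reader might also infer that the error would make albendazole look as if it had failed. The article does not support this. Its Sample size and Laboratory analysis sections tie clinical resistance to detecting helminths in a follow-up sample, and no egg-reduction threshold is set.

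**Reach.** The before-and-after prevalence tests, the cure rate and the paired t-test on Ct do not use the conversion, and Kato-Katz supplies EPG directly at all four samplings. It is also unclear how many before-and-after qPCR pairs will exist. Laboratory analysis turns to the Day 15 sample for the multiplex assay only when Day 0 is negative, whereas the Abstract describes testing positive samples at both times. These points stand and narrow the finding.

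**Conclusion.** The point holds in limited form. All four conversions are wrong as printed, by the article's own log10 description and its own slopes. That conclusion and the ceiling of 96 to 112 EPG need no assumption about observed Ct. Negative counts follow for any positive sample with Ct above about 35 to 37. The size and direction of the distortion in egg reduction do depend on Ct values that the article does not give, so the percentages above are illustrations, not predictions.

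The analyses at risk are the comparison of qPCR with Kato-Katz and the qPCR-derived intensity of infection. The detection-based resistance outcome is not affected.

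**What to change.** Write each conversion as EPG = 10^[(Ct − intercept)/slope], keeping the printed constants:

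- Ascaris: 10^[(Ct − 36.97)/(−3.489)]
- Trichuris: 10^[(Ct − 36.73)/(−3.288)]
- N. americanus and A. duodenale: 10^[(Ct − 35.02)/(−3.641)]

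Confirm that the analysis code uses this form. One test value suffices: Ascaris at Ct 25 should return about 2,696 EPG, not 34.3. Make the comparison with Kato-Katz on the log10 EPG scale, where the calibration is linear.

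The cost is four corrected formulas and a code check. No laboratory work, extra samples or change to the design is needed.
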